## 11.2 Sample size [14]

There is no formal sample size calculation and a total trial population of 240 patients is proposed. These numbers may reduce following review of interim analyses and feasibility assessment planned at 6 monthly intervals.

The Perioperative group is mechanistic, and it is envisaged to include 40 patients in each of the three clinical cohorts with 20 patients randomised to intravenous iron and 20 patients randomised to placebo (Cardiac, Vascular and Abdominal Surgery) totalling 120 patients.

The Recovery group is exploratory, and it is envisaged to include 40 patients in each of the three clinical cohorts with 20 patients randomised to intravenous iron and 20 patients randomised to placebo (Cardiac, Vascular and Abdominal Surgery) totalling 120 patients.

## 11.3 Participant retention and complete follow-up [18b]

Participants will be engaging in an outpatient clinic care. However, in our pilot audit, we had significant difficulty completing follow up with patients who lived in rural Western Australia due to the travel distance in order to attend more frequent follow up appointments. Participants will be given the opportunity to complete trial follow up on their scheduled medical or surgical outpatient clinic appointment days where possible.

## 11.4 Statistical Analysis [20a]

Analyses will be based on all randomised participants. Reporting of research findings will be in accordance with CONSORT guidelines. Baseline demographic data and other participant characteristics will be expressed as means and standard deviations for continuous variables and counts and percentages for categorical variables, with 95% confidence intervals provided for estimates of interest where appropriate. The differences in baseline characteristics will be evaluated by either $\chi^{2}$ or Fisher extract test for categorical variables and an independent samples t-test for continuous variables. Changes in recovery outcome scores will be compared for each participant as the difference between baseline and each specified time points scores with univariate analyses comparing changes in outcome.

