### 11.1.1 Primary Endpoint Change in Hb concentration from baseline to 90 days following randomisation

### 11.1.2 Secondary Endpoints Laboratory:

1. Change in Routine Iron markers
2. Changes in Experimental Iron markers
3. Changes in proteomic and metabolomic profiles.
4. Mental and physical recovery after surgery
5. Complication rate at 30 days post operation
6. Length of hospital stay
7. Re-operations
8. Unplanned re-admission to hospital for complications
9. Days Alive and at Home (DAH) 30 & 90
10. Change in clinical frailty score and activities of daily living (Nottingham extended ADL scale)
11. Changes in Sarcopenia
12. Changes in functional assessments
13. Changes in Quality of life

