**Methods for additional analyses (e.g. subgroup analyses)**

Each clinical cohort (Cardiac, Vascular and Abdominal surgery) will be assessed in a predefined subgroup.

**Methods in analysis to handle protocol non-adherence and any statistical methods to handle missing data** [20c]

Results will be analysed on an intention-to-treat basis. Secondary analysis will be per protocol.

**Plans to give access to the full protocol, participant level data and statistical code** [31c]

No later than 2 years after the collection of the final 6 month follow up assessments, we will deliver a completely deidentified data set to an appropriate data archive for sharing purposes.

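### Section 11.4 compares recovery scores by unadjusted change at each visit and tests baseline differences between randomised arms; a model adjusted for baseline and surgical cohort would be at least as precise

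*Protocol*

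**What the plan says.** All of this is in the Protocol.

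- **Outcome comparison (Section 11.4).** "Changes in recovery outcome scores will be compared for each participant". What is compared is the patient's change since baseline, one visit at a time, and the method is given only as "with univariate analyses comparing changes in outcome". No covariate, stratification factor or joint model over visits is named.
- **Baseline (Section 11.4).** "The differences in baseline characteristics will be evaluated by either" a chi-squared or Fisher test for categorical variables, with a t-test for continuous ones.
- **Primary endpoint (Section 11.1.1).** "Change in Hb concentration from baseline to 90 days following randomisation". No method of comparison is attached to it.
- **Cohorts (additional analyses, after Section 11.4).** "Each clinical cohort (Cardiac, Vascular and Abdominal surgery) will be assessed in a predefined subgroup". Cohort has no other stated use in the analysis.
- **Size (Section 11.2).** "There is no formal sample size calculation and a total trial population of 240 patients is proposed". Each of the two groups has three surgical cohorts, with 20 patients on iron and 20 on placebo in each.
- **Follow-up (Section 11.3).** In the pilot audit, "we had significant difficulty completing follow up with patients who lived in rural Western Australia". The text on missing data names only intention-to-treat and per-protocol analyses.

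**The concern.** These are choices that the Protocol states, so an analysis plan that follows its wording would inherit them.

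A raw change score fixes the weight on baseline at one, whatever the correlation with follow-up. Where the best weight is lower, this adds noise and carries chance baseline imbalance into the comparison through regression to the mean. Surgical cohort is built into the sample but not named as an adjustment factor, so any cohort difference in mean change stays in the error term. Comparing visits one at a time makes no use of a patient's other visits when one is missed, and the Protocol itself expects follow-up difficulty.

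Testing baseline differences between properly randomised arms tests a hypothesis known to be true. The p-values neither measure nor correct the effect of an imbalance on the outcome.

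The trial has 20 patients per arm in each cohort and no sample size calculation, so precision that can be had at almost no cost should not be given up.

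**Working it through.** **The plan's own figure.** 2 groups × 3 cohorts × (20 + 20) = 240, which agrees with Section 11.2. The Protocol gives no SD, effect size, power or baseline-to-follow-up correlation, so the inputs below are assumptions shown as ranges.

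**Precision of the two analyses.** Let the follow-up SD be 1, the baseline SD be k and their correlation be r. Per patient:

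- variance of the change score: 1 + k² − 2kr
- variance after baseline adjustment (ANCOVA): 1 − r²
- difference between them: (k − r)², which is never negative and is zero only when k = r

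So the change score cannot beat adjustment, apart from the one degree of freedom spent on estimating the slope. That cost is negligible at 60 per arm.

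*Equal variances (k = 1).* The ratio ANCOVA/change is (1 − r²) / (2(1 − r)) = (1 + r)/2.

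*Baseline SD 0.7 of follow-up SD (k = 0.7).* This is plausible for Hb because Section 6.2.1 admits only patients below 130 g/L (men) or 120 g/L (women), which truncates the baseline distribution. The ratio is (1 − r²) / (1.49 − 1.4r).

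| r | k = 1 | k = 0.7 |
| --- | --- | --- |
| 0.3 | 0.65 | 0.91/1.07 = 0.85 |
| 0.5 | 0.75 | 0.75/0.79 = 0.95 |
| 0.7 | 0.85 | 0.51/0.51 = 1.00 |

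A simulation with k = 1, 60 per arm and 4,000 runs gave change/ANCOVA variance ratios of 1.56, 1.33 and 1.16. The formula gives 1.54, 1.33 and 1.18.

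**In terms of power.** Take 60 per arm (one group of 120) and an effect that ANCOVA detects with 80% power at two-sided 5%. The change score then has power Φ(2.80 × √ratio − 1.96):

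- k = 1: 62%, 68% and 73% at r = 0.3, 0.5 and 0.7
- k = 0.7: 73%, 78% and 80%

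**Cohort.** If cohort explains 5 to 20% of the residual variance (assumed), leaving it out inflates the variance by 1/(1 − R²), that is by a factor of 1.05 to 1.25.

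**Chance imbalance.** Given a baseline difference d between arms, the change-score contrast is expected to be off by (r/k − 1)d. With k = 1 and r = 0.5 that is half the imbalance, in the opposite direction. Covariate adjustment removes it; a baseline p-value does not.

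**Baseline tests.** With 10 to 20 independent characteristics tested at 5% (assumed), the chance of at least one falsely significant difference is 1 − 0.95¹⁰ = 40% to 1 − 0.95²⁰ = 64%.

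**Is there a baseline to use?** For Hb, yes. Routine bloods are marked pre-operatively in the Perioperative schedule (Section 7.3) and at baseline in the Recovery schedule (Section 7.4.1). The frailty scale is also marked before treatment in both. For quality of life and function the Protocol disagrees with itself. The abstract's methods place these assessments at baseline for all participants, but the Perioperative schedule first marks them at discharge or day 8, after study drug. Under that schedule neither the stated change score nor baseline adjustment can be computed for those scores in that group.

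**The case against.** The strongest reply is that the quoted sentence covers recovery outcome scores only. No method is stated for Hb, a change endpoint can still be analysed with baseline as a covariate, and the analysis plan may do so. This stands in part: applying the univariate comparison to the primary endpoint is an inference. It is a natural one, since the endpoint is itself a change and no other method is given.

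Four stronger readings are tempting, but the Protocol does not support them:

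- *Baseline and cohort are discarded.* They are not. A change score subtracts baseline, and cohort is a predefined subgroup. Both are under-used.
- *Patients missing a visit are dropped, so the result is biased.* No complete-case rule is stated. Section 11.4 bases analyses on all randomised participants, and handling of missing values is commonly left to the analysis plan.
- *Each cohort gets its own significance test, so cohorts will appear to disagree by chance.* The subgroup sentence neither prescribes such tests nor excludes an interaction. A discordance rate would also need an SD that the Protocol does not give and the 8-week Hb difference from a different, preoperative trial.
- *The loss equals a fixed number of the 240 patients.* That needs equal variances, which the eligibility limits make doubtful for Hb. It also needs an analysis pooling both groups, which Section 11.2 does not state.

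It is also fair to say that the 20:20 split within each cell means cohort differences cost precision and do not bias iron against placebo. Baseline p-values alter no treatment estimate. Section 11.2 calls one group mechanistic and the other exploratory. These points limit the severity, but they give no reason to keep an analysis that is never better than the alternative.

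**Conclusion.** The point holds as one of efficiency and good practice; it does not threaten validity. Under randomisation with complete data the stated comparison is unbiased. Relative to baseline adjustment it loses about 0 to 35% of the information: 15 to 35% with equal variances and r from 0.7 down to 0.3, and 0 to 15% if the baseline SD is 0.7 of the follow-up SD. The direction does not depend on these assumptions, but the size does, and the Protocol gives no figures to narrow it. Omitting cohort may add to the loss.

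The baseline significance tests serve no purpose. The conflict over Perioperative quality-of-life and functional baselines is a separate obstacle, and it undermines the Protocol's own change score as much as the alternative.

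**What to change.** In Section 11.4:

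1. Replace the univariate change-score sentence with a model of the post-baseline value, for Hb and for each recovery score with a pre-treatment baseline. Adjust for that baseline value and for surgical cohort.
2. Fit it within each group (Perioperative, Recovery), or with group as a factor; the two visit schedules differ. Use the scheduled visits jointly, so that a patient who misses one visit still contributes.
3. Name the primary Hb contrast as iron minus placebo at the week-12 visit (84 days, window ± 2 weeks), the scheduled visit nearest to 90 days. Say from what date weeks are counted. The Recovery table marks randomisation under the 4-week column, whereas Section 7.4.2 places it after baseline assessment; these need to be reconciled.
4. Delete the baseline significance tests and describe the arms only.
5. Report cohort effects as estimates with confidence intervals from a treatment-by-cohort interaction.

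Before this, reconcile the abstract with the Section 7.3 schedule on whether Perioperative quality-of-life and functional scores have a pre-treatment baseline. If they do not, neither analysis can use one for those scores.

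The cost is a change of wording and slightly more analysis work. Hb needs no new data.

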**Methods for additional analyses (e.g. subgroup analyses)**

Each clinical cohort (Cardiac, Vascular and Abdominal surgery) will be assessed in a predefined subgroup.

**Methods in analysis to handle protocol non-adherence and any statistical methods to handle missing data** [20c]

Results will be analysed on an intention-to-treat basis. Secondary analysis will be per protocol.

**Plans to give access to the full protocol, participant level data and statistical code** [31c]

No later than 2 years after the collection of the final 6 month follow up assessments, we will deliver a completely deidentified data set to an appropriate data archive for sharing purposes.

## 11.5 Interim analyses [21b]

The data steering data monitoring committee will conduct an interim analysis 6 monthly intervals to assess feasibility of the trial recruitment and fidelity to the trial protocol.

# 12. Monitoring and Quality Assurance [23]

A trial specific monitoring plan will be established following a risk assessment and full details will be available. The trial will be monitored according to this agreed plan. Local investigators shall ensure that all study data are available for trial related monitoring, audits, and research ethics committee review.

# 13. Study Committees

## 13.1 Project Management Group (PMG) [5d]

The PMG will comprise the chief investigator, trial manager and research fellows responsible for managing the trial. The PMG will be responsible for the set up and day to day running of the trial. It will meet weekly during the planning stages of the study and less frequently when the study is recruiting.

## 13.2 Trial Steering Committee (TSC) [5d]

The TSC includes members of the PMG, experts in the fields of iron deficiency, as well as a lay representative. They will meet at regular intervals, not less than once a year. The TSC, in the development of this protocol and throughout the trial, will take responsibility for:

Major decisions such as a need to change the protocol for any reason Monitoring and supervising the progress of the trial Considering recommendations from the Data Safety and Monitoring Committee (DSMC) informing and advising the PMG on all aspects of the trial

## 13.3 Data Safety and Monitoring Committee (DSMC) [21a]

The DSMC includes three independent members including two medical experts and a statistician. Members of the DSMC cannot be investigators in the study or participate in other committees for this study. The role of the DSMC will be to monitor independently the safety of the study participants and to suggest amendments to this protocol if deemed necessary for reasons of patient safety or feasibility of study procedures. The DSMC members will meet early in the trial to establish a DSMC Charter. The chair of the DSMC reports to the chair of the TSC. To minimise potential bias, DSMC members will not have direct contact with the study site personnel or with participants.

# 14. Administrative Aspects

## 14.1 Ethical Considerations

This study will be conducted according to the Guidance for Good Clinical Practice E6 (R2) and in compliance with applicable laws and regulations. The study will be performed in accordance with the NHMRC Statement on Ethical Conduct in Research Involving Humans 2007 (updated 2018), the Australian Code for the Responsible Conduct of Research, 2018, and the principles laid down by the World Medical Assembly in the Declaration of Helsinki 2013.

## 14.2 Regulatory requirements

The study will be submitted for approval by the local regulatory authorities. SAEs will be notified according to the requirements of the local regulatory authorities.

## 14.3 Protocol amendments [25]

Changes and amendments must be submitted to HREC for review and approval. All Investigators are to conduct the study in accordance with the current protocol except when it is necessary to deviate to protect the safety, rights, and welfare of participant.

## 14.4 Publication policy [31a]

The PMG and TSC will oversee the publication outputs from this work. It is envisaged that the final protocol will be published in a peer reviewed journal and online either through the trial website or via the ANZCTR or Clinicaltrials.gov. The trial outcomes and results from this trial will be published in peer reviewed journals. In line with open access policy, all participants enrolling in the study will be asked if they wish communication of the results.

## 14.5 Archiving

The Investigator will be responsible for the retention of all trial documentation for 15 years or the appropriate retention period as stipulated by local regulations and ICH-GCP. Destruction of essential documents will require authorisation from the Sponsor.

**Supplementary Figure 1. Longitudinal haematological response.**

**Supplementary Figure 2. SF-36 T-score report**. The SF-36 is reported in 2 components: the physical component score (PCS) and mental component score (PCS). The T-scores for each component are derived from population norms and factor score coefficient weights obtained from data describing the Australian population reported in 2007[30].
